**Methods:**

This is a three-arm, parallel-group randomized controlled trial that will enroll 180 community-dwelling adults aged ≥ 65 years with MetS. Participants will be randomly allocated (1:1:1) to receive either omega-3 PUFA-enriched eggs, regular eggs, or no egg intervention (usual diet) for 12 weeks. Those assigned to the egg intervention groups will consume one boiled egg daily, five days per week. The control group will maintain their habitual dietary patterns without additional egg consumption. Biological samples (blood, urine, and stool) will be collected at baseline and weeks 4, 8, and 12. Plasma concentrations of omega-3 fatty acids, lipid metabolism indicators,inflammation and oxidative stress markers will be measured. Exploratory outcomes include comprehensive multi-omics profiling, encompassing metabolomics and gut microbiome will be tested.

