(1) Glucose metabolism and insulin resistance indicators: Measured markers will include fasting plasma glucose (FPG), glycated hemoglobin (HbA1c), fasting insulin, and C-peptide to assess glycemic control and pancreatic β-cell function. Additionally, the homeostasis model assessment of insulin resistance (HOMA-IR) will be calculated as: HOMA-IR = [FPG (mmol/L) × FINS (mU/L)] ÷ 22.5, where higher values indicate greater insulin resistance.(2) Metabolomics: This study will employ untargeted metabolomics to characterize the systemic effects of omega-3 PUFA-enriched egg intervention on metabolic phenotypes, aiming to identify potential metabolic pathways and biomarkers associated with primary clinical outcomes. Plasma, urine, and stool samples will be collected at baseline (Week 0) and follow-up visits (Weeks 4, 8, and 12), then stored at −80 C pending analysis. Metabolite features will be detected using liquid chromatography-mass spectrometry (LC-MS). To ensure reproducibility, standardized protocols adhering to the Minimum Reporting Standards for Metabolomics and Chemical Analysis Reporting Elements will be implemented throughout sample preparation, instrument operation, metabolite annotation, identification, and data preprocessing (26). Additionally, quality control samples will be incorporated to monitor analytical drift and batch effects, with corrections applied as needed to enhance data quality and comparability (27). Metabolomic results will provide exploratory mechanistic insights, which will be interpreted in conjunction with clinical phenotypes and findings from other omics analyses.(3) Gut microbiomics: Gut microbiota-related indicators will be evaluated as exploratory mechanistic outcomes to elucidate potential gut-derived mechanisms underlying metabolic phenotype changes (e.g., triglycerides) in older adults with metabolic syndrome following omega-3 PUFA-enriched egg intervention. Primary microbiome measures will include α-diversity, β-diversity, community structure comparisons, and analyses of differential microbial abundance and functional pathways.

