Stool samples will be collected at baseline (Week 0) and at Weeks 4, 8, and 12, and then stored at−80 C for subsequent analysis. The primary analytical endpoint will align with the clinical outcomes (Week 12), while samples collected at Weeks 4 and 8 will be analyzed to explore temporal changes and potential mechanisms. To ensure reproducibility and comparability, all procedures—including sample collection, storage, DNA extraction, sequencing, and statistical analyses—will follow standard operating procedures and reporting guidelines for human stool sample processing (28, 29).

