## Data entry and analysis

7

**Data entry:** Questionnaire data will be collected directly via electronic forms with built-in logic checks to ensure the accuracy and completeness of data entry, minimizing errors in data recording.

**Statistical analysis:** Statistical analyses will be performed using SPSS 24.0 and R 4.2.0 software. For baseline variables, continuous variables will be analyzed using one-way analysis of variance (ANOVA) or kruskal-wallis tests, while categorical variables will be analyzed using chi-square tests or Fisher's exact tests.

For longitudinal outcome measures, mixed-model repeated measures analysis of variance (MMRM) with an unstructured covariance matrix will be adopted as the primary analytical method. This model will include intervention group, time point, and group × time interaction as fixed effects, with subject-specific random intercepts. Pre-specified covariates (including age, sex, body mass index (BMI), baseline dietary intake, physical activity, baseline clinical parameters, and compliance) will be adjusted in the primary analysis based on their correlation with outcomes and clinical relevance.

Missing data will be handled using intention-to-treat (ITT) analysis with mixed models, which can accommodate unbalanced data under the missing at random (MAR) assumption. Sensitivity analyses will include complete case analysis and multiple imputation by chained equations (MICE) to verify the robustness of the results.

For multi-omics analyses (microbiome and metabolomics), Benjamini-hochberg false discovery rate (FDR) correction (*q* < 0.05) will be applied to control the expected proportion of false positives among the results. Microbiome data will undergo centered log-ratio (CLR) transformation to address compositional data constraints. Non-parametric methods [Friedman test, permutation-based multivariate analysis of variance (MANOVA)] will be used when the assumptions of normality or homogeneity of variance are violated. Principal coordinate analysis (PCoA) based on bray-curtis distances will be used to analyze microbiome composition, and principal component analysis (PCA) will be applied to metabolomics data. Associations between the microbiome and metabolome will be analyzed using sparse partial least squares (sPLS) or canonical correlation analysis (CCA), with FDR correction applied to ensure the reliability of the results.

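### The only univariate non-parametric fallback named for the omics data, the Friedman test, has no arm term; the Bray-Curtis input scale and the CCA option also need tightening (exploratory outcomes only)

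*Protocol article*

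**What the plan says.** The design is a "three-arm, parallel-group randomized controlled trial that will enroll 180 community-dwelling adults" (Abstract, Methods). On sampling, section 5.4 says "Stool samples will be collected at baseline (Week 0) and at Weeks 4, 8, and 12", with Week 12 as the main microbiome time point and Weeks 4 and 8 used to look at change over time. The same section classes metabolomics and gut microbiota as exploratory and says of the former: "This study will employ untargeted metabolomics to characterize the systemic effects".

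Section 7 (Data entry and analysis) first gives a mixed model for longitudinal outcomes with group, time and their interaction. A separate multi-omics paragraph then makes four statements that matter here:

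- Transformation: "Microbiome data will undergo centered log-ratio (CLR) transformation to address compositional data constraints".
- Fallback: "Non-parametric methods [Friedman test, permutation-based multivariate analysis of variance (MANOVA)] will be used when the assumptions of normality or homogeneity of variance are violated".
- Ordination: "Principal coordinate analysis (PCoA) based on bray-curtis distances will be used to analyze microbiome composition". The data scale that feeds the distance is not given.
- Microbe-metabolite association: "Associations between the microbiome and metabolome will be analyzed using sparse partial least squares (sPLS) or canonical correlation analysis (CCA"), with FDR correction added.

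**The concern.** The trial asks whether arms differ. Omics features are often skewed, so the fallback may be used often. If the univariate fallback is a within-participant test of time, the analysis moves from a question about arms to a question about visits exactly when the distributional assumptions fail. A shared drift over 12 weeks (season, trial participation, batch) could then look like a finding, and a true divergence between arms could be missed. The test also needs complete blocks, whereas section 7 chooses mixed models because they accommodate unbalanced data.

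Two further statements raise problems if taken literally. Bray-Curtis divides by the summed values of two samples, and that sum is zero for CLR data. Ordinary canonical correlation overfits badly when there are many features per participant, and an FDR step applied afterwards does not remove that.

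At stake is the mechanistic part of the trial, which Table 1 lists among the objectives and the Discussion presents as an innovation.

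**Working it through.** **Inputs.** From the article: 3 arms, N = 180 (60 planned per arm), 4 visits (k = 4), 25% dropout (section 2.3), so 180 × 0.75 = 135 completers. The plan prints no figure of its own on this point. Assumed for simulation: between-participant SD 1 and residual SD 1, time trends as stated below, and all feature counts.

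**1. Friedman test.** With R_j the sum over participants of the within-participant ranks at visit j,

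Q = 12 / [N k (k+1)] × Σ R_j² − 3N(k+1).

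For N = 180 and k = 4, 12 / (180 × 4 × 5) = 1/300 and 3 × 180 × 5 = 2700, so Q = Σ R_j² / 300 − 2700, on 3 degrees of freedom. Arm appears nowhere. Shuffling the arm labels leaves Q unchanged. Running the test inside each arm gives three time tests and still no comparison between them.

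Simulation, 1000 runs, pooled over arms, nominal 5%:

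| Truth | Test | Rejects |
|---|---|---|
| All arms rise 0, 0.2, 0.4, 0.6; no arm difference | Friedman | 99.7% |
| One arm +0.6, one −0.6 by the last visit, third flat | Friedman | 3.7% |
| As the row above | Kruskal-Wallis on change by arm | 99% |

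In the second case the rank sums cancel across arms, so the test stays near its nominal level although the arms diverge.

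Complete blocks: with the planned dropout, at most 135 of 180 participants remain. Intermittent missed visits lower this further.

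**2. Permutation-based MANOVA.** This can take arm as a factor. Its weakness is unequal dispersion, and that depends on arm size. Type I error at nominal 5% (Euclidean distance, 30 features, one arm with SD 1.5 times the others, 400 runs):

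| Arm sizes (more dispersed arm last) | Type I error |
|---|---|
| 60/60/60 | 5.8% |
| 66/60/54 | 10.5% |
| 52/50/33 | 15% |

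The Monte Carlo standard error at 5% is √(0.05 × 0.95 / 400) = 1.1 points, so the balanced case is compatible with 5%. Imbalance is plausible. The article specifies simple randomization; carried out as independent draws, the SD of an arm's size is √(180 × 1/3 × 2/3) = 6.3. Dropout adds to it.

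**3. Bray-Curtis on CLR values.** BC(x, y) = Σ|x_i − y_i| / Σ(x_i + y_i). CLR values are log x_i minus the mean log within the sample, so each sample sums to 0 and the denominator is 0 + 0 = 0. In 60 simulated samples of 200 taxa, 41% of CLR values were negative. One pair had numerator 656.75 and denominator 2.5 × 10⁻¹³, which is rounding error. All pairwise values were infinite or outside 0 to 1. On the untransformed proportions the same samples gave 0.60 to 0.85, which is well behaved.

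**4. Unregularised CCA.** After centring, the two feature sets span p and q dimensions of an (n − 1)-dimensional space. Once p + q exceeds n − 1 the spans intersect and the first canonical correlation is 1 whatever the data. On independent noise:

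| n | Features (assumed) | First canonical correlation |
|---|---|---|
| 180 | 10 + 10 | 0.39 |
| 180 | 50 + 50 | 0.89 |
| 180 | 90 + 90 | 1.00 |
| 180 | 200 + 500 | 1.00 |
| 135 | 200 + 500 | 1.00 |

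**The case against.** A reader might infer that the named methods cannot yield any valid comparison between arms. The article does not support that. Permutation-based MANOVA stands in the same bracket as Friedman and can compare arms. The mixed model with group-by-time is the primary method for longitudinal outcomes. PCoA is an ordination and sPLS or CCA an association method, so neither was offered as a test of arms.

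A reader might also infer that the ordination cannot be computed. The text never says that Bray-Curtis is applied to CLR values. CLR for feature-level tests and Bray-Curtis on proportions for beta-diversity is a coherent reading. On CCA, sPLS is named first and suits many features; no feature count is given, and filtering could reduce it. On Friedman, the sentence sits in the multi-omics paragraph and does not say that it replaces the mixed model for clinical outcomes; a within-participant time test has some use for describing Weeks 4 and 8. A condensed article may also leave details to a full plan.

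All of this stands and limits the point. It does not rescue Friedman, because the article positively names it, names no other univariate non-parametric method for follow-up data, and gives it no descriptive-only role. The missing Bray-Curtis scale also remains a real inconsistency, since the CLR sentence carries no restriction.

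**Conclusion.** The point holds in a limited form. The firm defect is that the only univariate non-parametric fallback named has no arm or arm-by-time term and loses every participant with a missed visit, a quarter or more under the plan's own dropout figure. The rejection rates of 99.7% and 3.7% rest on the assumed variances and trends. The absence of an arm term does not.

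The permutation-based MANOVA is usable; its sensitivity to unequal dispersion matters mainly when arm sizes differ. Two secondary points also hold: the Bray-Curtis input scale must be stated because the index is undefined on CLR values, and unregularised CCA should not stand as an open option. The size of the CCA problem depends on feature counts that are assumed here.

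The affected outcomes are exploratory. The primary triglyceride comparison does not depend on any of these methods. This is a correction worth making, of modest weight.

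**What to change.** In the multi-omics paragraph of section 7:

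1. Replace the Friedman test with the same mixed model (arm, time, arm-by-time) on log- or rank-transformed values. A rank test of change by arm is a simpler alternative at a single visit, though it also drops anyone missing that visit. If Friedman is kept, label it as a within-arm description of time.
2. For permutation-based MANOVA, name arm as the factor, permute at participant level so that repeated samples stay together, and report a dispersion test beside it.
3. Either use Aitchison distance (Euclidean distance on CLR values) for the ordination, or state that Bray-Curtis is computed on untransformed relative abundances.
4. For microbe-metabolite association, specify sPLS or regularised CCA, with cross-validation and permutation p-values before the FDR step.

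The cost is a few sentences and a little programming. No new data, visits or participants are needed, and Table 1 lists the trial as not yet recruiting, so the change can be made before any outcome is seen.

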### Sample size calculation

2.3

This three-arm randomized controlled trial will adopt an allocation ratio of 1:1:1. The primary outcome will be the change in fasting serum triglyceride (TG) levels from baseline to the end of the intervention. The main effect to be tested will be the difference in TG level changes between the omega-3 PUFA-enriched eggs intervention group and the regular eggs group. Based on previous dietary intervention studies in populations with metabolic syndrome, the estimated standard deviation of fasting serum TG is approximately 58 mg/dL (baseline TG level: 140.9 ± 58.0 mg/dL) (19). Sample size estimation will be based on data from a prior randomized trial, which reported a 35 mg/dL difference in triglyceride (TG) levels between participants consuming omega-3 PUFA-enriched eggs (152.476 mg/dL) and those consuming regular eggs (187.333 mg/dL) (20). Accordingly, the minimal clinically meaningful difference (δ) will be set at 35 mg/dL. Assuming a two-sided significance level of 0.05 and 80% statistical power (1–β = 0.80), the required sample size will be computed using the standard formula for comparing means between independent groups:

$$\begin{array}{l} N=\frac{2{\left(Z_{1-\frac{\alpha }{2}}+Z_{1-\beta }\right)}^{2}}{\delta^{2}} \end{array}$$

Where Z_1−α/2_ = 1.96, Z_1−β_ = 0.84, σ = 58 mg/dL, and δ = 35 mg/dL. Consequently, to meet the statistical power requirements for the primary comparison, approximately 44 participants per group will be needed. Considering a potential dropout rate of approximately 25% in 12-week dietary intervention studies among elderly populations (21), the sample size will increase accordingly:

$$\begin{array}{l} n=\frac{44}{1-0.25}\approx 59 \end{array}$$

Therefore, the final target sample size will be set at 60 participants per group, yielding a total of 180 participants across the three arms.

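### The FDR step for microbiome-metabolome associations has no p-values to act on under sPLS or CCA as named, and plain CCA on unreduced omics blocks finds near-perfect correlation in noise

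*Protocol article*

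**What the plan says.** Data entry and analysis sets one multiplicity rule for the multi-omics work: Benjamini-Hochberg "false discovery rate (FDR) correction (*q* < 0.05) will be applied to control the expected proportion of false positives among the results". It prepares the data as follows: "Microbiome data will undergo centered log-ratio (CLR) transformation to address compositional data constraints", and "principal component analysis (PCA) will be applied to metabolomics data". For the link between the two blocks it says: "Associations between the microbiome and metabolome will be analyzed using sparse partial least squares (sPLS) or canonical correlation analysis (CCA), with FDR correction applied". The same sentence gives this correction as what makes the results reliable.

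The article does not choose between the two methods. It names no regularisation, feature filter or dimension reduction ahead of CCA; PCA is mentioned for the metabolome, but not as input to CCA. It names no permutation, bootstrap or pairwise test for these associations. The permutation MANOVA in the same section is a fallback for violated assumptions and serves a different purpose.

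Section 5.4 fixes the metabolome as untargeted ("This study will employ untargeted metabolomics to characterize the systemic effects") and its role as exploratory ("Metabolomic results will provide exploratory mechanistic insights, which will be interpreted in conjunction with clinical phenotypes and findings from other omics analyses"). On size, Sample size calculation says "the final target sample size will be set at 60 participants per group, yielding a total of 180 participants across the three arms".

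**The concern.** A false discovery rate procedure takes p-values and returns a subset of them. If the analysis produces none for the associations of interest, the stated protection does not exist as written, whichever of the two methods is chosen.

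Both methods also search for the combination of taxa and the combination of metabolites that agree best in the sample at hand. With many features and few participants that search succeeds on unrelated data. Unvalidated in-sample results could therefore show strong associations where there are none, and readers would be told they were FDR-controlled. The Discussion presents the linked exposure, microbiota, metabolite and phenotype network as the study's methodological novelty, so these results are likely to be prominent in the trial's reports.

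**Working it through.** **Sample size.** Section 2.3 gives SD 58 mg/dL, difference 35 mg/dL, 1.96 and 0.84. Then 2 × (1.96 + 0.84)² × 58² / 35² = 43.06, so 44 per group. 44 / 0.75 = 58.7, so 59, set at 60, or 180 in total. The article's figures reproduce. With its 25% dropout, 180 × 0.75 = 135 completers. The article gives no figure for the sPLS or CCA analysis itself.

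**What FDR would act on.** sPLS output is a set of selected variables with loadings and component scores; it contains no p-values. Classical CCA with p and q variables allows at most min(p, q) tests, one per canonical dimension. These do not refer to taxon-metabolite pairs, and they are undefined when the dimensions exceed n. Benjamini-Hochberg therefore has no pairwise input unless another test is added.

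**CCA on CLR data.** Each CLR row sums to zero, so p parts have rank p − 1. With 50 parts at n = 180 the covariance has rank 49 and a condition number of about 6 × 10¹⁶, and plain matrix inversion fails. Dropping one part brings the condition number to about 180. The drop-one and generalised-inverse versions give the same first canonical correlation (0.745 on the same noise). The standard CCA routine in R uses a rank-aware decomposition and also runs, keeping 49 of the 50 columns.

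**CCA on noise.** After centring, n participants span n − 1 dimensions. Two blocks of dimension p − 1 (CLR) and q must share a direction, giving a correlation of exactly 1, once (p − 1) + q > n − 1. With 90+90 at n = 180, 89 + 90 = 179 = n − 1, which is the boundary. With 70+70 at n = 135, 69 + 70 = 139 > 134. Mean first canonical correlation between independent CLR noise and normal noise:

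| Features (taxa + metabolites) | n = 180 | n = 135 |
|---|---|---|
| 5 + 5 | 0.25 | 0.29 |
| 10 + 10 | 0.41 | 0.46 |
| 20 + 20 | 0.59 | 0.67 |
| 30 + 30 | 0.72 | 0.81 |
| 50 + 50 | 0.88 | 0.96 |
| 70 + 70 | 0.97 | 1.00 |
| 90 + 90 | 1.00 | 1.00 |

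With 50 CLR parts and 300 metabolite features at n = 180, every canonical correlation is 1. The feature counts are assumed.

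**sPLS on noise.** Assumed: 100 CLR taxa, 1,000 metabolites, 20 kept per block, one component. The mean in-sample component correlation is 0.73 at n = 180 and 0.78 at n = 135. The same loadings applied to fresh noise give about 0.05 and 0.06 in absolute value.

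**The case against.** Four points can be made for the plan.

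First, a reader might infer that the CLR transformation makes CCA impossible. It does not. The zero-sum constraint removes one redundant dimension and defeats only plain inversion. The article names R and does not prescribe inversion. This objection stands in full.

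Second, a reader might infer that a perfect correlation follows from the sample size alone. It follows from sample size together with feature count, and the article gives no count. With 10+10 reduced variables, noise gives 0.41 at n = 180, which is far from 1. This stands as a limit on the claim. Still, the metabolome is untargeted and no reduction before CCA is described, so combined dimensions above 135 to 180 are very likely if the blocks enter as measured. Counting the four visits as 4 × 180 = 720 independent rows does not remove the problem: noise then gives 0.68 with 100+100 features and 1.00 with 100+700.

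Third, the CCA arguments do not reach sPLS, the first-named option, which is built for more variables than participants. That is right. What reaches sPLS is the absence of p-values and the optimism of in-sample fit. The article does not say that in-sample correlations will be the reported evidence, so that second part is a risk and not a stated error.

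Fourth, tuning, fold structure and numbers of permutations are commonly left to a full analysis plan, and FDR correction is compatible with permutation p-values defined there. This also stands. The point raised here is narrower: the sentence pairs two named methods with a correction that neither can feed, and offers that correction as the guarantee of reliability.

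**Conclusion.** The concern holds in a limited form. For both methods, the promised FDR control over taxon-metabolite associations is undefined as written; this needs no assumption about feature counts. For CCA without regularisation or reduction, the result carries no information once the combined dimensions reach about n, and it is heavily inflated well before that. For sPLS, in-sample correlations of about 0.73 to 0.78 can arise from noise under the assumed 100 taxa and 1,000 metabolites with 20 kept per block, so they cannot serve as evidence without validation.

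The documents do not support saying that CCA cannot be computed here, that it must return 1 at this sample size, or that the trial will report spurious associations. The importance is moderate: these outcomes are labelled exploratory, and the primary triglyceride comparison is untouched.

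**What to change.** Replace plain CCA with sPLS or regularised CCA. Tune it by cross-validation at participant level, keeping all visits of one participant in the same fold. Report the out-of-sample component correlation with a permutation p-value obtained by shuffling participants.

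Name the p-values that enter Benjamini-Hochberg. They can be the permutation p-values of the components, or pairwise taxon-metabolite tests over all features that pass a stated filter applied without looking at the association. A short pre-listed set of pairs would not suit untargeted data.

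The cost is a few sentences and some computing time. The downside is that fewer and weaker associations will be reported. Table 1 lists the trial as not yet recruiting, so the change can be made before any data exist.
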